### Objectives {7}

The broad objective of this study is to use an experimental design to test two smoke-free policy compliance support interventions: (A) a “compliance through reduction (via relocation and reduction in personal smoking) and cessation” intervention targets households with smokers and involves support to shift smoking practices to designated areas and reducing personal smoking, and deliver in-residence smoking cessation support services via trained peer educators and (B) a “compliance through resident endorsement” intervention involving voluntary adoption of smoke-free living environments through personal pledges, visible door markers and/or via social media. We will compare randomly sampled participants in buildings that receive A or B or A plus B to the NYCHA standard approach.

We seek to achieve the following specific aims:

Aim 1: Experimentally test if compliance support interventions reduce personal smoking behavior.

Aim 2: Experimentally test if compliance support interventions reduce secondhand smoke exposure.

Aim 3: Determine if the tobacco retail environment surrounding each building moderates the relationship between compliance support interventions and smoking-related outcomes.

We hypothesize that the reduction/cessation plus resident endorsement intervention will yield significantly larger reductions in personal smoking and second-hand smoke exposure, compared to standalone interventions and the standard approach.

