### Trial design {8}

The trial design is a borough-stratified, four-arm, factorial-design, cluster RCT that targets 64 randomly selected buildings (16 buildings per arm) in separate NYCHA developments. We are recruiting and following 8 randomly selected residents stratified by smoking status − 4 smokers and 4 non-smokers - per building (n = 512) into four arms: (1) reduction/cessation, (2) resident endorsement, (3) reduction/cessation plus resident endorsement and (4) the standard approach (128 participants per arm) as shown in Fig. 1. A partnering community-based organization, Health People, Inc., specializing in peer-to-peer health education will train and supervise peer educators (PEs) who will then deliver the designated interventions. Quantitative assessments via survey questionnaire, salivary cotinine measurements, as well as sensory building observations will be used to measure outcomes. We will be evaluating the efficacy of compliance support interventions in reducing personal smoking and exposure to second-hand smoke in public housing. In addition, we will also determine if the tobacco retail environment surrounding a given public housing building moderates the relationship between compliance support interventions and smoking-related outcomes.

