#### Sample Size {14}

Power analysis was conducted using software PASS.15 for the primary outcome (change in salivary cotinine over a year) in Aims 1 and 2. Sampling 16 clusters (buildings) with 4 subjects per cluster (smokers for Aim 1, non-smokers for Aim 2) in each arm, we have 128 subjects per group or 256 in groups with or without a specific type of treatment (e.g. resident endorsement vs. no endorsement, cessation vs. no cessation). We calculated effect size as group mean difference in unit of standard deviation (SD) of the outcome, based on a two-sided test for mean difference between two groups in a cluster-randomized design with power of 80%. To compare groups with and without specific type of treatment, the group size of 256 may detect effect size of 0.283SD, 0.299SD, 0.312SD at significance level alpha = 0.05 for intra-cluster correlation coefficient r = 0.1, 0.15, 0.2, respectively. To compare intervention arms to the control arm, we have 3 comparisons and use conservative Bonferroni adjustment for multiple tests on significance level that alpha = 0.0167 (= 0.05/3). The sample size of 128 subject per arm may detect effect size of 0.472SD, 0.499SD and 0.524SD for r = 0.1, 0.15 and 0.2, respectively, at alpha = 0.0167. To put these numbers in perspective, using mean and SD estimated from a study of smokers in Maryland, an effect size of 0.283SD would correspond to a mean difference in salivary cotinine between the two intervention groups of 55.3 ng/mL with group SD = 195.4 ng/mL for smokers and of 0.19 ng/mL with group SD = 0.672 ng/mL for non-smokers.124 For instance a mean difference in 5 cigarettes smoked per day in the same study was 59.6 ng/mL for smokers.124 In England, following the smoke-free legislation salivary cotinine declined from mean level of 0.36 to 0.07 ng/mL (mean difference 0.29 ng/mL) among non-smokers.125 These findings support that we have sufficient power to estimate the impact of our interventions. The study is powered on an 80% retention rate, which we have achieved in other studies. Reasons for attrition will be tracked; those lost to follow up will be compared to the final sample.

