### Primary outcome

1)

Self-reported average number of cigarettes smoked per day and secondhand smoking exposure (hours of secondhand smoke exposure in the building in the past 7 days) will be measured at baseline (in person interview), 3 months (phone interview) and 12 months (in person interview). Salivary cotinine will be measured for 25% of the sample at baseline and at the 12-month follow-up for smokers to evaluate reliability of self-reported smoking behavior in Aim 1 and for non-smokers to evaluate self-reported secondhand smoke exposure in Aim 2.

To examine the intervention group differences in the change of self-reported smoking (Aim 1), we will use GLMRM with identity link, E(Yijkh) = ßh + ßkhtk + ßZij, where Yijkh is an outcome variable (transformed if necessary) for smoking exposure measured at time tk (t0 = 0 for baseline; t1 = 1 for 6 months, 0 else; and t2 = 1 for 1 year, 0 else) from the ith participant of the jth building in the hth arm/group (h = 1, 2, 3, 4). For the reference group of h = 4, ßk4 = 0 for k = 0, 1, 2; so that parameter ßkh (k = 1, 2; h = 1, 2, 3 for intervention arm) indicates the difference in outcome change since baseline between intervention group h and reference group, and ß is a vector of coefficients for the vector of control variables Zij (if any). To examine if effect of treatment A depends on treatment B or vice-versa, we will test null hypothesis ßk1 = ßk2 + ßk3 for all k, which suggests independent effects of treatment A and treatment B and simpler model that E(Yijk) = ß0 + ß1A + ß2B + ßk0tk + ßk1tk A + ßk2tk B + ßZij with dummy variables A and B indicating treatment type. To examine the intervention group differences in the change in hours of secondhand smoke exposure in the building in the past 7 days for non-smokers, we will use GLMRM with log link (Aim 2). Models will be run with and without control variables (if any).

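### The Aim 1 analysis is set up to drop to an additive model after a miswritten, low-powered interaction test, and no reported model is fixed in advance

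*Protocol article*

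**What the plan says.** Under Primary outcome, the protocol article gives a four-arm repeated-measures model for Aim 1. Each coefficient ßkh "indicates the difference in outcome change since baseline between intervention group h and reference group". To see whether A depends on B, "we will test null hypothesis ßk1 = ßk2 + ßk3 for all k", "which suggests independent effects of treatment A and treatment B and simpler model", and the additive equation with dummies for A and B follows. No significance level is given for this test, and the section does not say which of the two models is primary.

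Trial design {8} numbers the arms "1) reduction/cessation, (2) resident endorsement, (3) reduction/cessation plus resident endorsement and (4) the standard approach".

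Objectives {7} predicts that the combination "will yield significantly larger reductions in personal smoking and second-hand smoke exposure, compared to standalone interventions and the standard approach".

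Sample Size {14} gives figures for both kinds of comparison. For with-versus-without a treatment, "the group size of 256 may detect effect size of 0.283SD, 0.299SD, 0.312SD at significance level alpha = 0.05". For each arm against control the plan will "use conservative Bonferroni adjustment for multiple tests on significance level that alpha = 0.0167 (= 0.05/3"), and "The sample size of 128 subject per arm may detect effect size of 0.472SD, 0.499SD and 0.524SD for r = 0.1, 0.15 and 0.2". Neither comparison is made conditional on the interaction test, and no power is given for that test.

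**The concern.** A null that is not rejected is not evidence of independent effects, least of all when the test has little power. If the additive model then replaces the four-arm model on the same data, its A coefficient averages A without B and A on top of B. When the two interventions interact, that average is not the effect of A alone, and an interval computed as though the model had been chosen beforehand has the wrong coverage for A alone. The choice of model could also move the threshold, because the sample size section uses 0.05 for one family of comparisons and 0.0167 for the other.

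There is a second problem in the same sentence: the equation printed as the null is not the additivity condition for the arm numbering used elsewhere in the article.

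**Working it through.** **Inputs.** From Sample Size {14}: 16 buildings per arm with 4 smokers each (16 × 4 = 64), a stated 128 per arm, ICC 0.1 to 0.2, two-sided tests, 80% power. Assumed because not stated: a two-sided 5% level for the interaction test, outcome in SD units with equal variance across arms, one follow-up time.

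**Reproducing the plan's figures.** SE of a two-group difference = √(2(1 + 3·ICC)/n).
- Arm versus control, n = 128 as 32 buildings of 4, alpha 0.0167, noncentral t on cluster degrees of freedom: 0.472, 0.499, 0.524 SD for ICC 0.1, 0.15, 0.2. This matches the plan.
- With versus without, n = 256, alpha 0.05, normal approximation: 0.282, 0.298, 0.313 SD, against the stated 0.283, 0.299, 0.312.
- With 16 buildings of 4 (64 per arm), the same formulas give 0.685, 0.724, 0.760 and 0.399, 0.422, 0.443 SD.

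The stated figures therefore need twice the smokers per arm that the design recruits, so results for both 64 and 128 are shown below.

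**The null as printed.** Let a and b be the effects of A and B against control. Arm 1 is A, arm 2 is B, arm 3 is A+B. Under additivity ß1 = a, ß2 = b, ß3 = a + b, so the null should be ßk3 = ßk1 + ßk2. The printed contrast is ß1 − ß2 − ß3 = a − b − (a + b) = −2b. With truly additive effects and b = 0.283 SD its mean is −0.566 SD. Its SE is the interaction SE below, so it rejects 51% of the time at 64 per arm and 80% at 128.

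**Power of the corrected test.** Let v = (1 + 3·ICC)/n per arm. At ICC 0.1:

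| | 64 per arm | 128 per arm |
|---|---|---|
| v | 1.3/64 = 0.0203 | 1.3/128 = 0.0102 |
| SE, additive effect, √v | 0.143 | 0.101 |
| SE, arm vs control, √(2v) | 0.202 | 0.143 |
| SE, interaction, 2√v | 0.285 | 0.202 |
| Power, interaction 0.283 SD | 17% | 29% |
| Power, interaction 0.472 SD | 38% | 65% |
| Interaction for 80% power, (1.96 + 0.84) × SE | 0.80 SD | 0.57 SD |

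A 2-df test over both follow-up times, with the same interaction at each and an assumed correlation of 0.3 to 0.8, gives 14–18% and 33–44% at 64 per arm, so the one-time simplification does not drive the result.

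**If the test selects the model.** Estimate of A against control, with A alone truly null, ICC 0.1, 2,000,000 draws per case. The two error rates use 0.05 for both models, then 0.0167 for the four-arm contrast and 0.05 for the additive one.

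| n per arm | True interaction | Additive chosen | Overall bias | Type I error | 95% coverage |
|---|---|---|---|---|---|
| 64 | 0 | 95% | 0 | 6.4% / 5.5% | 93.6% |
| 64 | 0.283 SD | 83% | 0.083 SD | 16% / 15% | 84% |
| 64 | 0.472 SD | 62% | 0.092 SD | 26% / 24% | 74% |
| 128 | 0.283 SD | 71% | 0.066 SD | 23% / 21% | 77% |

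When the additive model is chosen with an interaction of 0.283 SD, its bias for A alone is half the interaction, 0.283/2 ≈ 0.141 SD. A four-arm contrast fixed in advance has 5.0% error at a nominal 5% and no bias, whatever the interaction.

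**The case against.** A reader might infer that the protocol lays down a rule by which the interaction test decides what is reported. It does not say so. The clause can be read as describing what the null means. The four-arm model is specified first and without condition, both families of comparison are sized, and the secondary-outcome models keep group and group-by-time terms. This stands, and it limits the claim to how the analysis is set up. What remains is that the article puts the test and the reduced model in sequence under the primary outcome.

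A reader might also infer that the A and B effects are biased whichever model is used. They are not. Without an interaction there is no bias and only slight size inflation. The larger figures need a true interaction, A alone as the target and, for the type I error, no effect of A alone. A averaged over B is a legitimate target that the sample size section plans for, and declaring it in advance would remove the pre-test problem equally well. Under additivity the reduced model even tests the standalone comparisons, because A+B against A is then B's effect. That last point depends on the very assumption the test cannot establish.

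**Conclusion.** The concern holds in a limited form. The printed null is wrong for the arm labels; that follows from the article alone. Once corrected, the test is too weak for non-rejection to support independence: 17% power for a 0.283 SD interaction at 64 per arm and 29% at 128, given the assumed 5% level, one time point and ICC 0.1. The bias of 0.083 SD (0.066 at 128), type I error of about 15–16% (21–23%) and coverage of 84% (77%) are conditional: the test must select the model, an interaction of 0.283 SD must exist, and A alone must have no effect. The finding covers Aim 1, the only aim for which the test is written. It should be put right before the data are analysed.

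**What to change.** - Correct the null to ßk3 = ßk1 + ßk2.
- Remove the step from non-rejection to the simpler model.
- Name the four-arm model as primary for Aim 1 in advance. This choice follows from the hypothesis in Objectives {7}, which sets A+B against each single intervention and the standard approach.
- State an alpha plan for all the contrasts this involves. There are five (three arms against control, and A+B against A and against B), while the Bonferroni adjustment in Sample Size {14} covers three.
- Report the interaction estimate with its interval, and the factorial main effects, as secondary results whatever the test shows.

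The cost is more than wording. The primary detectable effect becomes larger than for the factorial comparison: 0.472 against 0.283 SD at ICC 0.1 on the protocol's own figures, or 0.685 against 0.399 SD at 64 per arm. Spreading alpha over five contrasts rather than three by Bonferroni would raise it further.

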### Secondary outcome and Sensitivity analyses

1)

We will use GLMRM with logit or log links for binary or count outcomes, respectively, to evaluate group differences in the outcome changes from baseline to 3 and 12-month follow-up. The models will include predictors of dummy variables for time and group assignment as well as for group by time interaction as described above. Aim 1 (smoking behavior) secondary outcomes are whether smokers have successfully quit (binary), the mean number of quitting attempts (continuous). Aim 2 (exposure to secondhand smoke) secondary outcomes include ever observing someone smoking indoors within the building in the past 7 days (both smoker and non-smoker participants) (binary), hours of secondhand smoke exposure in the building in the past 7 days (count), number of people smoking and number of cigarette butts in common areas of the building (count).

Differential effect of the tobacco retail environment. The impact of differential tobacco retail environments (e.g., retailer density) around each building will be systematically evaluated for the primary outcomes and for quantitative secondary outcomes listed in Aims 1 and 2. The tobacco retail environment will be measured at the longitude-latitude point coordinate of each building using a geographic kernel density estimate with standard bandwidth to estimate the square mileage density of tobacco sellers in the surrounding area for each specific building point coordinate. This information is publicly available from the City of New York. As continuous metrics, these kernel density estimates will be separated in tertiles and at median breaks and the relationships tested in Aims 1 and 2 will then be tested within separate levels of tobacco retail density. We will also extend the GLMRM with identity or log link for each outcome variable in Aims 1 and 2 by adding the factor for retail environment, its interaction with group, time, and group by time interaction. In addition to the analysis for effect of a pre-specified modifier (the retail environment), we will conduct several a priori subgroup analyses to explore potential differential effect of the interventions in the continuous outcomes by age, sex, knowledge, and attitude towards the policy.

We will evaluate reliability of self-reported measures of active and passive smoking and revisit the primary analyses adjusting for potential imperfect reliability using regression calibration approaches.

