The second stage of enrollment is at the resident level. Participants must be (1) able and willing to provide verbal informed consent, (2) at least 18 years old, (3) able to communicate in English or Spanish, (4) living in the building at least 5 days/week and 9 months/year, and (5) not planning to move in the next 2 years. Participants who (1) have severe physical or mental medical conditions (e.g., cognitive disability) or other factors that could limit participation or ability to give informed consent in the study at baseline or during follow-up visits, (2) participate in focus groups conducted pre or concurrently as RCT that are geared towards understanding how to improve intervention arms for greater impact (buildings identified for focus groups are buildings that will not be assigned an intervention or have recruitment conducted for the main study), or (3) only smoke non-tobacco products (e.g., marijuana) are excluded from participating in the study due to the focus of the study on tobacco products. It should be noted that during the period of recruitment, the smoke-free policy in NYCHA was modified to also include marijuana use. In anticipation of this modification to the smoke-free policy, we are collecting preliminary information regarding marijuana use.

Recruitment of NYCHA residents will be conducted via door knocking and lobby intercepts until the targeted number per group is reached (4 smokers, 4 non-smokers in each building). Smoker status is defined as smoking a tobacco product including e-cigarettes at least 5x/month, and nonsmoker status is defined as never having smoked any product or quit smoking at least 12 months prior to recruitment.

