#### Secondary outcomes

There are 6 secondary outcomes being measured:

We will evaluate change in number of participants with successful quit attempts measured at baseline assessment, interim assessment, and long-term assessment for smokers.We will evaluate change in number of quit attempts using the mean number of quitting attempts among smokers measured at baseline, interim, and long-term assessments.We will evaluate change in number of participants with second-hand smoke observations who have either observed second-hand smoking or not measured at baseline, interim, and long-term assessments.We will evaluate change in number of hours of second-hand smoke exposure via self-reported number of hours of observing someone smoke indoors measured at baseline, interim, and long-term assessments.We will evaluate change in number of smokers via counted number of people observed smoking in common areas at building visits.We will evaluate change in number of cigarette butts via counted number of cigarette butts observed in common areas at building visits.

These outcome measures are summarized in Figure 5.

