## Data collection and management

### Plans For Assessment And Collection Of Outcomes {18a}

There are three assessments during this trial. These include a baseline assessment conducted upon recruitment and after building randomization, an interim assessment conducted over the phone approximately 3 months after the delivery of intervention, and a final long-term assessment conducted approximately 12 months after the delivery of intervention. The survey questionnaire collects information on housing conditions, indoor air quality, personal smoking behavior and cessation attempts, exposure to secondhand smoke, opinions on secondhand tobacco exposure, the smoke-free policy and tobacco policies, and health conditions. Additionally, passive drool samples from 25% of participants (n = 128) is collected at the time of the baseline assessment and at the final follow-up. Sensory building observations occur at the start of recruitment and during the final assessments to record signs of active smoking and/or tobacco/marijuana odor. The presence of cigarettes, cigars, ashtrays with/out ashes, matches or lighters will be documented within apartments and around the building premises including stairwells, elevators, hallways, laundry rooms, in/outdoor community spaces, playgrounds, and the perimeter of the buildings.

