### Aim Specific

We will use generalized linear models with repeated measures (GLMRM) for each aim where outcome variables may have different form (continuous, binary or count) and the measurements are likely to be correlated due to residing in the same building or being from the same participant over time. The models use various link functions to relate outcome to linear combination of predictors. For example, identity link for continuous outcome is linear model with repeated measures and logit link for binary outcome is logistic model with repeated measures. We will use the generalized estimation equation method to estimate model parameters and make statistical inference since it takes into account intra- cluster (within-building or within-person) correlations and uses all available data.

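### If quitting means current status, the quit outcome's change-from-baseline log-odds coefficients have no finite estimate, because every smoker enters unquit; follow-up comparisons survive but are not named as the effect

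*Protocol article*

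**What the plan says.** All references are to the Protocol article.

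- *Secondary outcome and Sensitivity analyses* uses logit or log links for binary or count outcomes "to evaluate group differences in the outcome changes from baseline to 3 and 12-month follow-up". It continues: "The models will include predictors of dummy variables for time and group assignment as well as for group by time interaction as described above". The first outcome it lists is "whether smokers have successfully quit (binary").
- *Aim Specific* fixes the form ("logit link for binary outcome is logistic model with repeated measures") and estimation by generalized estimating equations (GEE), keeping every available record. Baseline rows are therefore in the model.
- *Primary outcome* (statistical methods) codes baseline as the reference time and reads the group-by-time coefficient as an arm's change from baseline minus the control arm's change. The secondary outcomes inherit this.
- *Secondary outcomes* describes the endpoint as "change in number of participants with successful quit attempts measured at baseline assessment, interim assessment, and long-term assessment for smokers".
- *Eligibility Criteria {10}*: "Smoker status is defined as smoking a tobacco product including e-cigarettes at least 5x/month". People who stopped at least 12 months earlier enter as non-smokers.
- *Plans For Assessment And Collection Of Outcomes {18a}* takes the baseline assessment at recruitment and makes the 3-month assessment a telephone contact. It adds: "Sensory building observations occur at the start of recruitment and during the final assessments".

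**The concern.** A change in log-odds from baseline needs a baseline proportion strictly between 0 and 1. The entry rule and the outcome together suggest that the baseline proportion who have quit is exactly zero in every arm. If so, the coefficient that carries the intervention effect does not exist as a finite number. Software will still print something, often with a convergence flag set to true, and the printed value can depend on the iteration limit and the working correlation. Someone would then have to choose another contrast after seeing the data, on an outcome that bears directly on the cessation intervention.

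The same umbrella sentence also covers the counts of people smoking and of cigarette butts in shared areas. For these it asks for a change to 3 months, a time at which no building observation is scheduled.

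**Working it through.** **Inputs.** From *Trial design {8}*: 4 arms, 16 buildings per arm, 4 smokers per building, so 16 × 4 = 64 smokers per arm and 256 in all. From *Sample Size {14}*: 80% retention, so 0.8 × 64 = 51.2, about 51 per arm at follow-up. The article gives no quit rate and no power figure for this outcome, so there is no stated figure to reproduce. For illustration only, follow-up quit rates were assumed: 5–6% control, 6–8% endorsement, 10–12% reduction/cessation, 14–18% combined.

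**Algebra.** Let p(h,k) be the proportion quit in arm h at visit k, with arm 4 the control. The group-by-time coefficient is

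[logit p(h,k) − logit p(h,0)] − [logit p(4,k) − logit p(4,0)].

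With p(h,0) = p(4,0) = 0, both baseline logits are minus infinity and the expression is infinity minus infinity. The intercept goes to minus infinity and the time effects to plus infinity.

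The follow-up contrast, group + group-by-time, equals logit p(h,k) − logit p(4,k). The baseline terms cancel, so it is finite whenever both outcomes occur in both cells.

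**Counting.** Coefficients: 1 intercept + 3 group + 2 time + 6 group-by-time = 12. Cells with a non-degenerate outcome: 4 arms × 2 follow-up visits = 8. The design restricted to those rows has rank 8. None of the 12 coefficients is individually estimable as coded, but the 8 arm-by-visit log-odds are.

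**One simulated trial**, with every smoker unquit at baseline.

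Ordinary logistic fit of the three-visit model:

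| Iteration limit | Intercept | Group-by-time SE |
|---|---|---|
| 10 | −11.6 | 35 |
| 25 | −26.6 | 62,954 |
| 60 | −37.6 | about 11.9 million |

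The printed group-by-time coefficient for the combined arm at 3 months is 1.33 at 25 iterations and 1.65 at 60. Adding the group coefficient restores the same contrast each time: 0.00 + 1.33 = 1.33 and −0.32 + 1.65 = 1.33.

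GEE clustered on building, three visits:

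- Independence working correlation: group-by-time SEs of about 2,300 to 2,900. The follow-up log odds ratios are still recoverable, with SEs of about 0.6 to 0.9.
- Exchangeable working correlation: group-by-time SEs above 100,000, and one group coefficient with no computable SE. The follow-up contrasts have the same point values, but their SEs were 17.9 for one and not computable for the other five.

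GEE on the 3- and 12-month records only: all 8 coefficients are finite with ordinary SEs. The combined-versus-control log odds ratio at 3 months is 1.33 (SE 0.64), and the control intercept is −3.01 (SE 0.55).

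The divergence comes from the zero baseline, not from the assumed quit rates.

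**Residual risk after the fix.** With 51 smokers in a cell, treated as independent, the chance of no quitters is 0.95^51 ≈ 7% at an assumed 5% quit rate and 0.90^51 ≈ 0.5% at 10%. An empty cell would bring back the same separation in that cell.

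**Building counts.** The model section asks for change to 3 and to 12 months. The assessment section schedules building observations twice, at the start of recruitment and at the final assessment. Only the baseline-to-12-month change can be computed.

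**The case against.** A reader might infer that the planned model has no estimable parameters and that the treatment comparison on quitting is lost. The documents do not support that. The between-arm odds ratios at 3 and 12 months are linear combinations of the same model, and they equal what a follow-up-only fit gives. Nor is any particular software symptom, such as every standard error coming back missing, a property of the plan; the output varies with settings.

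The zero baseline is also inferred, not stated. *Secondary outcomes* lists "successful quit attempts measured at baseline assessment, interim assessment, and long-term assessment for smokers", so a baseline value was expected, and nothing defines successful. A history item (a past quit followed by relapse) would give a non-zero baseline and an ordinary fit. The smoker definition also counts e-cigarettes, so if quitting refers to cigarettes only, some enrolled smokers could score as quit at entry. This stands as a condition on the finding. The wording in the model section favours current status. If a history item is meant, the outcome list and the model section need reconciling instead.

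A reader might also take quitting to be the main secondary outcome. The article lists six without ranking them, and no power calculation rests on this one.

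On the building counts, the outcome list promises only counts at building visits, so the fault is loose umbrella wording. It still asks for something the schedule cannot supply.

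Finally, a condensed article may leave detail to an analysis plan. Here, though, the article itself states the link, the terms, the reference time and the target contrast; the objection is to what it states.

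**Conclusion.** The point holds in limited form. Reading successfully quit as current status, and with all enrolled smokers current users at baseline, the six group-by-time coefficients that the article treats as the intervention effect have no finite estimate. Their printed values and standard errors depend on software. Eight of the 12 dimensions survive, including every between-arm odds ratio at 3 and 12 months, but the article does not name these as the effect. The damage is confined to one of six unranked secondary outcomes and is repairable without new data. It should still be corrected before analysis, because a model rule that cannot deliver its named contrast invites a choice made after seeing results. The conclusion rests on the current-status reading; the simulated figures rest on assumed quit rates and only illustrate it.

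The building-count mismatch is separate and does not depend on that reading.

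**What to change.** 1. Define successfully quit: which products it covers, and whether it is current status.
2. For that outcome, fit the logit model to the 3- and 12-month records only, with arm, visit and arm-by-visit terms, clustered on building. Name the between-arm odds ratio at each visit as the effect.
3. Remove change from baseline for this outcome in *Secondary outcomes* and in *Secondary outcome and Sensitivity analyses*.
4. State in advance that a penalised or exact method will be used if any arm-by-visit cell has no quitters.
5. For counts of people smoking and of cigarette butts, limit the change to baseline to 12 months, with one record per building per visit.

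The cost is wording only: no new data, visits or participants.
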